#### Mixed Methodology

Triangulation mixed methods quantitative and qualitative data analysis will be used to evaluate quantitative and qualitative data [97]. Using an explanatory sequential mixed methods design, qualitative data collection and analysis will increase the investigators’ understanding of participant experiences of the tailored material for both cultural relevance and relevance to living with HIV.

#### Quantitative Data

Quantitative data analysis will focus on (1) behavioral markers of engagement with the app (ie, completion of >75% of all assigned videos and completion of >75% of all assigned exercises); (2) self-report evaluations of the app including ease of interacting with the app (ie, >75% of all participants agreeing that MASP+ is easy to use based on a rating of ≥3 on the scale), that the MASP+ features (eg, automated treatment messages that follow EMA and treatment videos) are useful and helpful on a similar scale, and that at least 75% of participants would be likely to recommend the app to a friend; and (3) data from the System Usability Scale [98-100]. Low engagement and evaluation of MASP+ will be discussed with each participant during the qualitative interview.

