#### MASP+ Feedback

We assess the perceived utility of MASP+ using the standardized System Usability Scale (a participant-completed, reliable, and valid metric for measuring usability and acceptability of technologies), which is administered during a 6-week follow-up survey [84-86]. Using a 5-point Likert-type scale (1=strongly agree to 5=strongly disagree), participants indicate their level of agreement with statements about the app’s usefulness (eg, “I thought the smoking cessation app was easy to use”).

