##### Random Sampling

Twice each day during weeks 1 to 6 and week 28, participants are prompted to complete EMAs that are scheduled to occur randomly during each participant’s normal waking hours. Participants rate their affect by indicating their level of agreement with several statements on a 5-point scale from “strongly disagree” to “strongly agree” (eg, “I feel stressed”). In addition, participants are asked about smoking triggers (eg, “I have an urge to smoke”), current depression level (“Rate your current level of depression [feeling sad]”), and anxiety level (“Rate your current level of anxiety [feeling nervous]”). Participants are also asked to describe their current environment (eg, home and work) and social setting.

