### Sample Size Determination

As this is the first empirical evaluation of the MASP+ intervention in this population, our focus is on determining the feasibility of the new intervention and obtaining preliminary estimates of effect sizes on smoking and HIV outcomes and the hypothesized mechanism of change, rather than conducting a full-scale and statistically powered examination of comparative efficacy. We expect that MASP+ will be superior to the NCI QuitGuide on all outcomes examined, but that the effects of MASP+ may vary and be larger for smoking outcomes than for HIV outcomes. On the basis of power calculations conducted using Repeated Measures and Sample Size and simulation studies identifying the sample sizes necessary to detect indirect effects [105,106], a target sample size of 72 would provide sufficient statistical power to detect a medium to large effect (Cohen *d*≥0.6) and an indirect effect for H3 if the treatment effect on AS is large (Cohen *d*=0.8) and the effect of AS on outcomes is medium to large (Cohen *d*=0.5). Our conclusions will primarily be based on effect sizes and associated CIs, and the effect size estimates (and associated CIs) from this trial will be used to guide future larger trials of comparative efficacy.

Qualitative interviews are conducted with all MASP+ and QuitGuide participants. The recommended minimum size for any subgroup is 20 interviews [107]. However, based on our prior work [48], interviews vary substantially in the content provided, so interviews will be conducted with all enrolled study participants in MASP+ and QuitGuide to meet the saturation of key study questions. Interviewing all MASP+ participants should be sufficient for the saturation of key study questions. The QuitGuide interviews will be used as a comparative group following the analysis of the MASP+ content, based on our prior work.

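### The ease-of-use benchmark counts ratings of 3 or more as agreement, which conflicts with the only app-evaluation scale whose anchors the protocol gives (1 = strongly agree, 5 = strongly disagree)

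*Protocol article*

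**What the plan says.** Under Data Analyses, Quantitative Data, the protocol article lists three groups of quantitative data: (1) behavioural engagement with the app, (2) self-report evaluations of the app, and (3) the System Usability Scale.

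Element (2) contains the benchmark: ">75% of all participants agreeing that MASP+ is easy to use based on a rating of ≥3 on the scale". It then asks that the MASP+ features "are useful and helpful on a similar scale", and that at least 75% would be likely to recommend the app to a friend. Element (3) is listed on its own as "3) data from the System Usability Scale".

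The MASP+ Feedback section describes the System Usability Scale and gives its response format: "Using a 5-point Likert-type scale (1=strongly agree to 5=strongly disagree), participants indicate their level of agreement with statements about the app’s usefulness". The example item is "I thought the smoking cessation app was easy to use".

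One other agreement scale appears, under Random Sampling: a "5-point scale from “strongly disagree” to “strongly agree" format. It is for momentary affect ratings, not for evaluating the app.

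**The concern.** The benchmark equates a rating of 3 or more with agreement. On the printed app-evaluation anchors, agreement lies at 1 and 2, 3 is the midpoint, and 4 and 5 are on the disagreement side. The word for agreement and the numeric cut-off therefore cannot both stand if those anchors apply. Because the usefulness and helpfulness items refer to a similar scale, they inherit the problem.

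Feasibility is a stated focus of the pilot (Sample Size Determination), and the quantitative results are to be combined with the interviews to refine MASP+ before a larger trial (MASP+ Feedback: Qualitative Interviews). An acceptability threshold that reads in the wrong direction, or that treats indifference as approval, would mislead that refinement. This goes beyond detail left to an analysis plan: a percentage, a cut-off and a scale direction are all printed, and they do not fit together.

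**Working it through.** **Step 1: put the cut-off on the possible scales.**

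| Scale | Ratings counted by ≥3 | Agree categories |
|---|---|---|
| 1 = strongly agree to 5 = strongly disagree (as printed in MASP+ Feedback) | 3 (midpoint), 4, 5 | 1, 2 |
| 1 to 5 coded the other way (not stated for app evaluation) | 3 (midpoint), 4, 5 | 4, 5 |
| 0 to 4 ascending, or 1 to 4 ascending (not stated for app evaluation) | top two categories | top two categories |

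On the first scale the rule is inverted. On the second it counts neutral answers as agreement. Only on the third kind of scale is it right as written.

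**Step 2: inputs for the size of the effect.**

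- Target sample size 72 (Sample Size Determination). Equal arms and complete response at week 6 are assumed, giving n = 72 / 2 = 36 MASP+ respondents.
- Passing requires more than 75%. Since 0.75 × 36 = 27, at least 28 of 36 are needed (28/36 = 77.8%).
- The response distributions below are illustrative assumptions. The protocol gives none.

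**Step 3: probability of passing.** With p the true share counted by the rule, P(pass) = Σ from k = 28 to 36 of C(36, k) p^k (1 − p)^(36 − k).

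*Printed anchors (1 = strongly agree):*

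| Assumed distribution on ratings 1/2/3/4/5 | Share ≥3 | P(pass), rule as written | Share ≤2 | P(pass), counting 1–2 only |
|---|---|---|---|---|
| Favourable: 45/40/10/3/2% | 15% | about 0 | 85% | 0.92 |
| Unfavourable (mirror image): 2/3/10/40/45% | 95% | 0.9999 | 5% | about 0 |
| All neutral | 100% | 1 | 0% | 0 |

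*Reverse-coded 1 to 5 (5 = strongly agree), with 50% agreeing, 30% neutral and 20% disagreeing:* the share at ≥3 is 50% + 30% = 80%, so P(pass) = 0.716, although only half agree. Counting 4 and 5 only (50%) gives P(pass) = 0.0006.

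**Step 4: sensitivity to the number of respondents.** At n = 72, 0.75 × 72 = 54, so at least 55 are needed. The pattern is the same: about 0 for the favourable sample and 1.0000 (to four decimals) for the unfavourable one under the rule as written, and 0.82 for the reverse-coded example.

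There is no figure in the plan to reproduce here, because the protocol states a threshold and not a calculated quantity.

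**The case against.** The strongest reply is that the conflict rests on a link the text does not make. The Quantitative Data section lists the System Usability Scale as element (3), apart from the self-report evaluations in element (2), and the printed anchors are given only for that instrument. Element (2) covers ease of interacting with the app, usefulness of its features and recommending it to a friend. These topics match the week-6 interview described under MASP+ Feedback: Qualitative Interviews, whose items are not shown. The ratings could come from there, on another scale. The protocol itself uses a 0 to 4 format for anxiety sensitivity; on an ascending scale of that kind, or an ascending 1 to 4 scale, a cut-off of 3 would be correct.

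This stands, and it makes both the inversion and the counting of neutrals conditional. It does not clear the text. No such scale is stated for app evaluation, and Table 2 lists no app-rating survey other than the System Usability Scale and the interview. The printed example item concerns ease of use, which is what the benchmark tests. On any 1 to 5 scale the cut-off is wrong, whichever way the scale runs.

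Three stronger readings should be resisted:

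- A reader might infer that a well-liked app will certainly fail and a disliked one will pass. That follows only if the System Usability Scale anchors govern element (2).
- A reader might infer that the denominator deliberately includes QuitGuide participants. A benchmark about rating MASP+ most naturally refers to those who received it; the wording is loose and could say so.
- A reader might infer that the trial's conclusions are at risk. No progression decision is tied to this benchmark, conclusions are to rest mainly on effect sizes and confidence intervals, and item-level ratings could be re-cut at analysis.

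**Conclusion.** The point holds in conditional form. The benchmark's cut-off conflicts with the only app-evaluation anchors the protocol prints, and the two sections must be reconciled. If those anchors apply, the rule is inverted: with 36 respondents, 85% agreement passes with probability about 0 and 95% neutral or disagreeing passes with probability 0.9999. If the item is on a 1 to 5 scale coded the other way, the rule is too lenient: 50% agreement with 30% neutral passes with probability 0.716. If element (2) uses an undefined 0 to 4 or ascending 1 to 4 scale, the cut-off is right and only the description is missing.

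The probabilities rest on assumed response distributions, equal arms and complete response. The mapping of the cut-off to the anchors needs none of these assumptions. Severity is modest: it concerns an acceptability benchmark of a feasibility pilot and leaves the primary abstinence analysis untouched.

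**What to change.** In the Quantitative Data section:

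- Name the instrument behind element (2), print its anchors and state any reverse-coding.
- Define agreement as the agree categories only: 2 or less on the anchors in MASP+ Feedback, or 4 or more if the item is reverse-coded on 1 to 5. If another instrument is used, define agreement by its own agree categories.
- Apply the same rule to the usefulness and helpfulness items.
- Take the more-than-75% share among MASP+ participants who answered the item, not as a fixed count. For example, 36 respondents would need 28, but 30 would need 23 (0.75 × 30 = 22.5).

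The cost is a few sentences and a check of the data coding, with no new data collection. The downside is that the benchmark is harder to meet than one that counts neutral answers. Settling it before the ratings are analysed avoids choosing the cut-off after seeing them; the article reports 9 participants enrolled at submission.

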Upon completion of the baseline survey and receipt of the baseline package, the participants complete a randomization call with the study staff. During the randomization call, the participants are randomized to receive the MASP+ or QuitGuide interventions based on the randomization chart developed by the study statistician ([name]). Block randomization was used and stratified according to binary sex (assigned at birth). Variable-sized permuted block randomization (block sizes vary from 4 to 12) is used. Before data analyses, the balance of randomization will be checked and controlled for imbalanced factors by including any factors that differ between groups as covariates. The participants are provided with a unique code to access the app to which they are randomized. MASP+ participants have access to all MASP+ features (ie, Treatment Videos, Coping Toolkit, Quit Tips, and Stress Management Trainings) through the Insight platform. Participants randomized to the control intervention (ie, QuitGuide) have access to limited features (ie, App Instructions, Payment Tracking, Call Staff, and Record Stress) through the Insight platform and receive intervention content (ie, Track My Craving, Manage My Mood, and Learn To Quit) through the QuitGuide app. Participants assigned to the control intervention receive assistance with downloading the QuitGuide app through the Google Play Store. Both intervention groups use the Insight app to complete the study assessments, which include the baseline survey, weekly follow-ups, the 28-week follow-up, and EMAs. Once the code is entered, the research staff orients the participant to the app features and the iCO carbon monoxide (CO) breath testing device. Participants have access to MASP+ or QuitGuide content through the final follow-up (ie, the 28-week follow-up). At the end of the randomization call, participants are directed to take a brief postrandomization survey, which must be completed within 6 days after the randomization call. Failure to complete the postrandomization survey within 6 days does not affect participants’ status in the study.

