#### Smoking Outcomes

During each weekly follow-up survey, smoking status is biochemically confirmed using the Insight platform and the Bedfont Scientific iCO smokerlyzer device. Biochemically confirmed 7-day point prevalence abstinence (PPA) at 26 weeks postquitting date is the primary study outcome. This is consistent with best practices as well as most published smoking cessation RCTs (refer to the clinical practice guidelines) [54,67]. In their baseline package, participants receive the Bedfont iCO smokerlyzer, which they use to verify smoking status at each weekly follow-up assessment (weeks 1-6 and week 26 postquitting date). At the end of each assessment, the participants are directed by the Insight app to connect the iCO device to the smartphone (simply by pressing the power button on the device) and complete the iCO test. The date and time of completion are collected and saved to our server along with the test results. Our CO criteria are informed by numerous studies that have used CO cutoffs of <7 ppm [68-74]. The CO level is a validated indicator of smoking status and outcomes and is strongly correlated with cotinine and other biochemical measures that have longer detection windows [75-77].

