#### MASP+ Feedback: Qualitative Interviews

Participant experience is assessed via a Zoom-based qualitative interview conducted at the end of treatment (week 6). The semistructured qualitative interview is conducted by trained members of the research team and audio recorded. These interviews focus on the ease of interacting with the app, the usefulness of app features, how the app can be improved, how sociocultural factors that affect Black smokers with HIV could be further woven into the intervention, and their willingness to refer the app to a friend. As participants in both study arms use the Insight app to complete EMAs and receive intervention content via the Insight app or QuitGuide app, the qualitative interview questions primarily concern participants’ experiences with Insight (MASP+ and EMA, or EMA only) and QuitGuide (intervention content). During the qualitative interviews, participants provide details about the features of the different apps that they did and did not like (eg, “What did you like about the app?”), how app features impacted relevant study outcomes (eg, “Which, if any, app features helped you manage your HIV better?”), and how the app or apps they used could be improved (eg, “How can we make the app fit better with your life experiences?”). Combined with the primary outcomes and other quantitative data, qualitative interview data will be used to refine MASP+, which will then be tested in a large-scale RCT.

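### The week-6 interview raises low use and low ratings of MASP+ with no matching topic stated for QuitGuide, a possible arm-specific prompt before the week-28 primary endpoint

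*Protocol article*

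**What the plan says.** All references are to the protocol article.

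- **The instruction.** Data Analyses, Quantitative Data: "Low engagement and evaluation of MASP+ will be discussed with each participant during the qualitative interview". The engagement markers listed just before it are "completion of >75% of all assigned videos and completion of >75% of all assigned exercises". These are MASP+ features. The ease-of-use target in the same paragraph also names MASP+.
- **When and by whom.** MASP+ Feedback: Qualitative Interviews: "Participant experience is assessed via a Zoom-based qualitative interview conducted at the end of treatment (week 6"), and "The semistructured qualitative interview is conducted by trained members of the research team and audio recorded".
- **Which arms.** Sample Size Determination: "Qualitative interviews are conducted with all MASP+ and QuitGuide participants". Table 2 gives 24 interview items for MASP+ and 20 for QuitGuide.
- **Access after the interview.** Recruitment and Procedures: "Participants have access to MASP+ or QuitGuide content through the final follow-up (ie, the 28-week follow-up"). The same section describes monthly check-ins between weeks 6 and 28 that remind all participants of the features available to them.
- **Endpoint.** Smoking Outcomes: "Biochemically confirmed 7-day point prevalence abstinence (PPA) at 26 weeks postquitting date is the primary study outcome".
- **Purpose.** Recruitment and Procedures and the interview section present the interview as a way to learn about participants' experience and obtain suggestions for improving the app.

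**The concern.** The trial compares an app that the Conclusions call fully automated with another app. A research team member who raises a person's low use of the experimental app, while that person can still open it, may prompt renewed use. If this happens in one arm only, the week-28 comparison contains a component that belongs to neither app, and no planned analysis could separate it out. Descriptions of app use after week 6 would be affected in the same way.

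This deserves attention in a pilot because Sample Size Determination says the conclusions will rest mainly on effect sizes and confidence intervals, which will then guide larger trials. The point estimate is what the next trial will use.

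**Working it through.** The plan gives no figure for this point, so there is none to reproduce. The check compares the sections with one another.

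**1. Timing.** The interview is at week 6. The primary assessment is 26 weeks after the quit date, which is 28 weeks after baseline. The gap is 28 − 6 = 22 weeks, and app content is available throughout.

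**2. What is common to both arms.** The staff-led interview at week 6, questions about liked and disliked features and possible improvements, app access to week 28, and the monthly feature reminders.

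**3. What is stated for one arm only.** The discussion of low engagement and low evaluation. It names MASP+, and its markers are MASP+ videos and exercises. QuitGuide participants use a version of Insight with the MASP+ features removed (NCI QuitGuide Condition), so the topic as worded cannot apply to them. No equivalent about low use of QuitGuide appears in the article.

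**4. What does not separate the arms.** The example question "Which, if any, app features helped you manage your HIV better" is given for interviews in general, not for MASP+ alone. The 24 versus 20 items show a longer MASP+ guide but say nothing about prompting.

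**5. How many people.** Assuming 1:1 allocation, 72 / 2 = 36 in the MASP+ arm. This is an upper bound: if only low users or low raters have the discussion, fewer are involved.

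**6. Sensitivity of the estimate, with assumed counts.** The article gives no expected abstinence rate and no effect for such a discussion, so these counts only illustrate scale. One person in 36 is 1/36 = 2.8 percentage points. The odds ratio is [b/(36 − b)] / [a/(36 − a)], with a QuitGuide and b MASP+ quitters. The standard error of its logarithm is √[1/a + 1/(36 − a) + 1/b + 1/(36 − b)].

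| QuitGuide | MASP+ | Odds ratio | 95% CI |
|---|---|---|---|
| 4/36 | 4/36 | 1.00 | 0.23 to 4.35 |
| 4/36 | 5/36 | 1.29 | 0.32 to 5.26 |
| 4/36 | 6/36 | (6/30)/(4/32) = 1.60 | 0.41 to 6.23 |
| 7/36 | 7/36 | 1.00 | 0.31 to 3.21 |
| 7/36 | 8/36 | 1.18 | 0.38 to 3.70 |
| 7/36 | 9/36 | (9/27)/(7/29) = 1.38 | 0.45 to 4.22 |

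One or two quits more or fewer would move the point estimate visibly but leave it well inside the sampling uncertainty. Nothing in the article says that the discussion would change even one outcome.

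**The case against.** The case on the other side is substantial.

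- **Human contact is balanced.** Every QuitGuide participant is also interviewed by staff. A reader might infer that MASP+ participants receive a staff conversation and QuitGuide participants receive none. The article does not support that; only one topic within the interview differs. This stands.
- **No coaching is described.** The stated purpose is feedback, and discussing low engagement can simply mean asking why use was low. Airing complaints about an app need not increase its use. A reader might infer a booster that favours MASP+, but that is conjecture about both effect and direction. This stands.
- **Nobody is contacted because of low use.** Interviews are scheduled for everyone, and the article does not say whether interviewers see individual usage data. This stands.
- **It comes late, among common prompts.** The 6-week active period has ended, most scheduled content has been delivered, and both arms then receive monthly reminders. This makes a lasting difference less likely. It does not remove the asymmetry, because on-demand content remains open and the reminders are the same in both arms.
- **The interview guide is not shown.** It may already put an equivalent question to QuitGuide users. That is possible, and it limits the point to what the article states. The instruction as written still names only MASP+.
- **The topic serves the design.** Mixed Methodology specifies an explanatory sequential design, in which quantitative results inform the interviews. Deleting the topic, or hiding usage and ratings from interviewers, would work against it. This stands, and the fix therefore keeps the topic.

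**Conclusion.** The point holds in a limited form. The plan writes in a discussion of low MASP+ engagement and evaluation at week 6, states no counterpart for QuitGuide, and leaves both apps open until the primary endpoint 22 weeks later. That is a potential arm-specific prompt of unknown size. The documents do not show that it acts as a prompt, that it would favour MASP+, or that it would affect the HIV outcomes.

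The conclusion rests on reading the instruction as confined to MASP+, which its wording supports, and on the absence of an equivalent for QuitGuide in the article. The figure of about 36 people assumes 1:1 allocation and is a maximum. Severity is minor: this is a pilot with wide intervals, and the asymmetry is one interview topic. It is worth correcting because the correction costs almost nothing.

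**What to change.** Keep the topic and make it the same in both arms. Replace the sentence in Quantitative Data, and align the interview guide, along these lines: *At the week-6 interview, all participants will be asked, in the same neutral words, about reasons for any low use or low rating of their assigned app (MASP+ or QuitGuide). Interviewers will gather information only and will not encourage use or remind participants of features.*

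This preserves the link between quantitative results and interviews. It also gives the planned comparison of QuitGuide with MASP+ responses (Qualitative Data) a like-for-like basis on this topic. Nine participants were enrolled at manuscript submission, so record the date of the change; any interviews held under the earlier guide can then be identified.

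The cost is a small edit to the guide, one protocol sentence and a slightly longer QuitGuide interview. No visits or staff are added.
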